### Data collection

Subjects will be contacted to schedule a visit with the clinical team for screening evaluation. During the screening session, each subject will undergo the Mini Mental State Examination (39), Tinetti’s Scale (40), Barthel Index (41) and the IADL scale (42). Once the compliance with the study’s inclusion and exclusion criteria are verified and the informed consent is obtained, the team will proceed with the baseline assessment. As this is a pilot study, no sample size calculation is planned; pilot studies typically involve a limited number of participants — in this case, 12.

At baseline, demographic data will be collected, the Positive and Negative Affect Schedule (PANAS) and the SF12 questionnaire will be administered to evaluate participants’ quality of life. Furthermore, participants will undergo the Montreal Cognitive Assessment (MoCa) to assess cognitive status.

At follow-up, participants’ evaluation will be assessed by means of Positive and Negative Affect Schedule (PANAS), the SF12 questionnaire and the Montreal Cognitive Assessment (MoCa). Satisfaction with the project will be evaluated through two structured questionnaires administered to both participants and their caregivers.

The assessment will be carried out at the beginning and at the end of each quarter (see Figure 1).

The scales which will be used during the evaluations are described below.

### Mini-mental state examination

The Mini-Mental State Examination (MMSE) is a brief screening tool developed as a clinical method to assess and grade cognitive impairment. The total score ranges from 0 to 30. Scores ≥24 are considered indicative of the absence of Major Neurocognitive Disorder (MND), scores between 18 and 23 suggest a mild stage of MND, scores between 11 and 17 indicate a moderate stage, and scores ≤10 are associated with severe MND. The raw score is adjusted based on the subject’s age and educational level (39).

### Tinetti’s scale or performance-oriented mobility assessment

Tinetti scale is a tool used to evaluate balance and gait performance. The test is clinically used to determine the mobility status of a subject or to assess changes in balance and gait time. The total POMA (POMA-T) consists of two sub-scales: the balance evaluation scale (“balance scale” or POMA-B) and the gait evaluation scale (“gait scale” or POMA-G). Scores equal to or <1 indicate a non-ambulatory subject, scores between 2 and 19 indicate a walking subject at risk of falling, scores equal to or greater than 20 indicate a walker with a low risk of falling (40).

### Barthel index

The Barthel Index is a questionnaire for systematically assessing Activity of Daily Living which asks about 10 basic ADLs (for example, personal hygiene, food intake, and toilet use). The maximum score of 100 indicates most independence, with a score of 0 indicating complete dependence in performing basic ADLs (41, 43).

### Instrumental activities of daily living scale (IADL)

The Instrumental Activities of Daily Living (IADL) scale assesses functional abilities in older adult individuals that are considered essential for maintaining independence. These activities include using the telephone, shopping, preparing meals, housekeeping, doing laundry, using transportation, taking medications, and managing finances. Each activity is scored from 0, indicating dependence, to 1, indicating independence. The total score ranges from 0 to 8 for women and from 0 to 5 for men, as three of the listed activities are traditionally not considered applicable for male respondents (41).

### Positive and negative affect schedule (PANAS)

The Positive and Negative Affect Schedule (44) is a measure of self-reported affect which assess the two most general emotional dimensions that describe affective experience and subjective well-being. The PANAS consists of two scales which are composed of 10 items each: the Positive Affect scale (PA) reflects the level of pleasant engagement (e.g., feeling enthusiastic, excited, active and determined) and the Negative Affect scale (NA) reflects a general dimension of individual distress (e.g., feeling scared, nervous, guilty and ashamed). The PANAS scales show excellent psychometric properties.

### Short form health survey (SF12)

The 12-item Short Form health survey, SF-12 (45–47), is a measure of health-related quality of life. It is an instrument with different weights for scoring physical and mental health, and measures health-related quality of life with 12 items categorized in eight areas: physical functioning, role physical, bodily pain, general health, vitality, social functioning, role emotional, and mental health. The raw scores of each item are coded, weighted, and summed into two scales: physical component summary score (PCS) and mental component summary score (MCS). Algorithms to calculate the value of the PCS and MCS indices of the SF-12 are available (47). Higher scores indicate better quality of life. The instrument will be used as in interviews.

### Montreal cognitive assessment (MoCA)

The Montreal Cognitive Assessment is a rapid short screening test (5–10′) widely used to assess mild cognitive impairment (48). It assesses multiple cognitive domains: executive functioning, attention, language, memory, visuospatial skills, and orientation. In Italy, the MoCA has been adapted and standardized (49, 50). It offers the possibility of calculating both a total score and subscores for each domain. Standardized norms are available for both the total score and the domain-specific subscores.

### Participants satisfaction ad hoc questionnaires

The first questionnaire consists of two items evaluated using a three-point Likert scale represented by a series of three facial expressions, ranging from a sad face (score = 1, “not very satisfied”) to a happy face (score = 3, “very satisfied”). The first item assesses the participants’ level of appreciation for the activities carried out during their stay on the farm. The second item evaluates whether the participants perceived a positive social and relational environment within the farm, and whether this made them feel welcomed and at ease. This questionnaire provides an important subjective measure of participant satisfaction and will be administered at the end of each three-month cycle of activity.The second questionnaire is designed to assess the participant’s overall satisfaction either at the conclusion of the project or at the time they decide not to continue participating in the subsequent cycle of activities. It consists of six items. The first three are evaluated using a Likert scale ranging from 0 to 10, where 0 represents the lowest score, 10 the highest, and 5 a neutral score. These items investigate: (1) how the participant evaluates the overall experience and the reasons behind their rating; (2) whether they perceive any changes in their physical condition; and (3) whether they notice any changes in their emotional or mental well-being since participating in the project. The remaining three items are open-ended questions designed to gather more in-depth feedback. These questions explore the participant’s general comments, the reasons that led them to take part in the project, and any suggestions for improving its organization (e.g., timing, activities, or other aspects).

### Caregivers satisfaction ad hoc questionnaire

The questionnaire is designed to assess the satisfaction of the informal caregiver at the end of the entire project or in any case when the subject decides not to participate in the activities in the following quarter. The questionnaire is composed of six items. Three of them are assesses with a Likert scale from 0 to 10 where 5 is the neutral score, 0 is the worst score and 10 is the best score. The items concern: how the caregiver evaluates the experience of his/her loved one in the project and why; if they observe any change in the physical conditions and then in the emotional or mental conditions of their loved one compared to before starting to participate in the project activities. The other three items are open questions on more general comments, on what prompted the caregiver to have their loved one participate in the project and if they would change something in the organization of the project itself (time, activities, other).

### Ad hoc sheet on “treatment monitoring”

In order to evaluate and, if necessary, redefine the individualized activity plan developed for each patient, a dedicated has been created to enable continuous quantitative and qualitative assessment. The *ad hoc* sheet “Treatment monitoring” will be filled out by the facilitator based on constant observation of the participant during the activities in the farm.

The quantitative section of the observation sheet evaluates the following parameters: interest, communication, enjoyment, and mood. Each of these factors is assessed using a 5-point Likert scale, where 1 represents the lowest level (e.g., “no interest,” “did not communicate during the meeting,” “did not show enjoyment,” “very low mood”) and 5 indicates the highest level (e.g., “showed a lot of interest,” “communicated very well during the meeting,” “had a lot of fun during today’s session,” “very good mood, appeared relaxed and happy”). This scale allows for a nuanced understanding of the participant’s engagement and emotional state throughout the activities.

Furthermore, the facilitator will have the opportunity to qualitatively note in it the significant elements of participation in the individualized treatment with a description of the events and emotional behaviors of the user like as level of participation, concentration, boredom, and behaviors of distancing from the activity. The form concludes by asking the facilitator to identify the Montessori markers that define the daily activities conducted with each individual. Examples of Montessori markers include, for instance, the assessment of the participant’s emotional state upon arrival at the farm, opportunities to exercise free choice during activities, the repetition of proposed tasks to support learning and independent execution, responses to external distracting stimuli, and the facilitator’s need to implement strategies to support concentration.

### Follow-up evaluation

The follow-up survey will take place at the end of the 3-month intervention and constitutes the final phase of the first cycle of prototype implementation. All measures from the initial screening will be repeated to check for any changes in the participants’ condition. In particular, it will be noted whether the subjective well-being has increased since the first survey, so whether the positive affects has increased and negative affects has decreased and if quality of life as increased. Moreover, it will be noted whether the participants and their caregivers are satisfied with the project through two *ad hoc* satisfaction questionnaires. This evaluation will be useful in order to identify any changes likely to improve the intervention.

Finally, after the three implementation cycles, the number of subjects who participated in one or more project cycles and the number of subjects who abandoned the project and the reasons for such dropouts will also be evaluated.

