### Study population

For the purposes of this pilot study, a limited number of participants will be selected to evaluate this intervention for this type of subject and to assess the feasibility of the intervention and participant satisfaction. The sample therefore consists of 4 participants for each of the three farms involved in the study, for a total of 12 participants overall. According to the literature, this is the maximum number of individuals with MCI that can be accommodated on each farm under the exclusive supervision of non-healthcare facilitators. Eligible participants are male or female and at least 55 years of age at the time of baseline assessment. These subjects can only be included in the study if they have a diagnosis of MCI (26, 27).

Exclusion criteria are applicable to participants who have a more severe level of cognitive impairment and physical conditions that prevent participation in farm activities (e.g., severe visual impairment and motor deficits). The active participation in another research study is also an exclusion criterion.

All eligibility criteria at the time of baseline assessment are summarized in Table 1.

**Table 1 tab1:** Eligibility criteria.

Inclusion criteria
55 years of age or older;
male and female;
diagnosis of mild cognitive impairment (MCI);
Mini Mental State Examination ≥ 24;
ability and willingness to sign informed consent.
Exclusion criteria
Mini Mental State Examination <24;
severe visual impairment;
inability to walk without help or assistance, Tinetti’s scale <20;
refusal to provide informed consent;
participation in another intervention study.

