Therefore, project activities will be customized to fit the cognitive capacity and specific characteristics of the individual and to encourage active engagement and direct contact with the social and physical environment. The Montessori principle of “free choice” will be the one that will most inspire the entire project. In particular the person first will have the possibility to choose whether to join the project or not and then, throughout the course of the project, the person will always have the possibility to choose the level of commitment and the way of participation. The proposal of activities by the facilitators will be inviting and not coercive and the activities can also be proposed directly by the subjects involved. Furthermore, the activities will be designed as a stimulus to maintain and strengthen daily life skills by making people feel useful in pursuing a common goal within the farm. For example, people will be asked to take care of plants, collect vegetable and fruits for lunch, visit to farm animals, prepare labels for farm-stored food, and so on. Some activities will be repeated over time, albeit at an increasingly difficult level, in order to offer the subject, the possibility of learning them and carrying them out independently. Another key element drawn from the Montessori approach will be the continuous and attentive observation by the facilitator which allows the definition of an individualized plan of activities that are adequately stimulating and significant for the person (23). Based on observational data, the facilitator can adapt the difficulty of the tasks, encourage commitment, foster conditions for success and modify the proposed activity if the ongoing one does not align with the individual’s characteristics and preferences.

For the first time, the principles of the Montessori program will be adapted from the residential care context to an agricultural setting where individuals are in direct contact with nature, animals and the daily farm routines. This work of extrapolation and re-adaptation, as well as any element related to the application of Montessori principles to the project was curated by the Montessori International Centre of Perugia.

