### Statistical analysis

Data will be expressed by mean and standard deviation for continuous variables and by frequency and percentages for categorical ones.

Comparisons of all the scale variables of interest in the time (baseline vs. 3 months follow-up) will be performed using paired samples t test. We could also categorize some scales using specific cut-off and could evaluate if there has been a change of category over time by chi-square test for example.

Statistical significance will be set at *p* < 0.05.

All analyses will be performed using IBM SPSS Statistic for Windows, Version 24.0 (IBM Corp., Armonk, NY, USA).

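### The article plans no 3-month PANAS, SF-12 or MoCA for people who leave during the first cycle, so the paired t test on affect describes first-cycle completers and can flatter the programme

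*Protocol article*

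**What the plan says.** The design is a single arm with "4 participants for each of the three farms involved in the study, for a total of 12 participants overall" (Study population). On size, Data collection states "As this is a pilot study, no sample size calculation is planned". The primary outcome is positive and negative affect, measured by PANAS; SF-12 and MoCA are secondary (Measures and outcomes, Table 2). Data collection places assessments at the start and end of each quarter.

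The analysis is fixed in one sentence of Statistical analysis: "Comparisons of all the scale variables of interest in the time (baseline vs. 3 months follow-up) will be performed using paired samples t test". The threshold follows: "Statistical significance will be set at *p* < 0.05".

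On people who leave, Follow-up evaluation says that, after the three cycles, "the number of subjects who abandoned the project and the reasons for such dropouts will also be evaluated". Exit questionnaires on satisfaction go to participants at the end of the project or "at the time they decide not to continue participating in the subsequent cycle of activities", and to caregivers on the same trigger. Each has a 0-10 item on perceived emotional or mental change.

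On freedom to participate, the Montessori approach section says that "the person will always have the possibility to choose the level of commitment and the way of participation".

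**The concern.** A paired t test needs two scores per person. Someone who stops in the second month and is not asked for the 3-month scales drops out of the comparison.

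That loss need not be random here. Participation is voluntary throughout, by design. A person who does not enjoy the days may well be the one who stops coming, and enjoyment lies close to the primary outcome, affect. There is no control arm in which a similar loss would show up. If the people with the poorest change are the ones missing, the mean change among those left is too favourable.

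This matters because Limitations says that user feedback on satisfaction and well-being will guide adjustments so that the service can take more participants.

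Attendance raises a related point. Facilitators score engagement from what they observe during farm activities, so those ratings can cover attended days only. High ratings read differently at full attendance than at half.

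**Working it through.** **1. The plan's own figure.** 4 participants × 3 farms = 12, as stated. The article gives no power, SD or dropout rate, so there is nothing further to reproduce.

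**2. Who is missing from the stated test.**
- *Leaves during cycle 1:* has a baseline score; no section states that a 3-month score will be sought; excluded from the pairs.
- *Finishes cycle 1 and then stops:* is due the end-of-quarter scales under Data collection; has both scores; not affected.
- *Continues:* has both scores; not affected.

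Only loss before the 3-month assessment matters for this test.

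**3. Size of a possible bias.** Assumptions, none of them from the article: true mean change 0; changes normal with SD 1, signed so that positive is improvement; k of the 12 leave before month 3; the leavers are the k lowest on a score that correlates r with their own change. The test is taken as two-sided at 0.05, since sidedness is not stated.

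The expected mean change among completers is then

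bias = r × (mean of the upper 12 − k expected normal order statistics for n = 12).

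That mean is 0.274 for k = 2, 0.393 for k = 3 and 0.509 for k = 4. The table gives the bias in SD of change, with the simulated probability of a significant improvement in brackets (200,000 trials per value of r):

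| r | k = 2 | k = 3 | k = 4 |
|---|---|---|---|
| 0 | 0 (2.5%) | 0 (2.5%) | 0 (2.5%) |
| 0.3 | 0.08 (4.4%) | 0.12 (5.2%) | 0.15 (6.0%) |
| 0.5 | 0.14 (6.4%) | 0.20 (8.4%) | 0.25 (10.3%) |
| 0.7 | 0.19 (9.6%) | 0.27 (13.9%) | 0.36 (18.2%) |

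For example, r = 0.5 and k = 3 gives 0.5 × 0.393 = 0.20. With k = 0 the bias is zero for any r.

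**4. Loss of precision.** Even if leaving is unrelated to change, fewer pairs cost power. The standardised mean change detectable with 80% power (noncentral t, two-sided 0.05) is 0.89 with 12 pairs, 1.00 with 10 and 1.16 with 8.

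**The case against.** A reader might infer that leavers are merely counted and never measured. The article does not support that. Reasons are recorded, and participants and caregivers who decline the next cycle complete an exit form that asks about perceived emotional change. Those people have also reached the end of a quarter and are due PANAS, SF-12 and MoCA. The gap is confined to people who leave within the first cycle. For them the exit form would not help the stated test in any case: it is not PANAS and has no baseline.

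A reader might also infer that the bias grows at 6 and 9 months. The only comparison stated is baseline against 3 months, so no later test exists to be biased.

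Third, the bias is possible, not shown. The article gives no dropout rate and no link between leaving and affect. People may leave because of illness or transport, and the Montessori approach section argues that free choice makes refusal less likely. This stands, and it is why the size can be given only as a range that starts at zero.

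Fourth, rules for missing data and sensitivity analyses commonly sit in a full protocol or SAP, neither of which is shown. This stands too: their absence is not the point. The point is whom to ask for the scales at 3 months, because no later analysis can recover a PANAS that was never taken.

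Finally, the feasibility list in Measures and outcomes is introduced as inclusive, so it does not rule out reporting attendance. Attendance is therefore a suggested addition and not an error in the plan.

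**Conclusion.** The point holds in a limited form. As written, the 3-month affect result applies to people who complete the first cycle, and it can be biased in the programme's favour if those who leave earlier are doing worse. The bias is zero if nobody leaves before month 3 or if leaving is unrelated to change. With 2 to 4 of 12 leaving selectively and r between 0.3 and 0.7, it is about 0.08 to 0.36 SD of change, and the false favourable rate is about 4% to 18% instead of 2.5%. The dropout numbers, the correlation and the absence of a true effect are all assumptions. In a small uncontrolled pilot this is a modest correction, but it is worth making before data collection because it changes what is collected.

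**What to change.** 1. State that PANAS, SF-12 and MoCA will be sought at the planned 3-month date from everyone enrolled who agrees, regardless of attendance, and include these people in the paired comparison.
2. Where 3-month scores are still missing, label the t test a completer analysis. Report the number of completers out of 12, and the baseline scores of leavers and stayers side by side.
3. From the facilitator's individual daily record (Staff dedicated to reception), report sessions attended out of sessions offered beside the engagement ratings.

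An analytic repair is no substitute for the first step. Setting leavers' change to zero multiplies the completers' mean by (12 − k)/12. With 3 leavers and r = 0.5 that is 0.20 × 9/12 = 0.15, which removes only a quarter of the bias. A mixed model, which the article does not plan, would not remove the bias either when leaving depends on a change that was not observed.

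The cost is a short extra questionnaire contact for a few people, and a count from records already kept.

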### Statistical analysis

Data will be expressed by mean and standard deviation for continuous variables and by frequency and percentages for categorical ones.

Comparisons of all the scale variables of interest in the time (baseline vs. 3 months follow-up) will be performed using paired samples t test. We could also categorize some scales using specific cut-off and could evaluate if there has been a change of category over time by chi-square test for example.

Statistical significance will be set at *p* < 0.05.

All analyses will be performed using IBM SPSS Statistic for Windows, Version 24.0 (IBM Corp., Armonk, NY, USA).

